### After phase sample size

For the before phase, no sample size is required and eligible patients during the study period will be recruited. The sample size was calculated with the intent of estimating uncertainty of outcomes, to inform the design of the future cluster trial. Our previous work suggested that the combined outcome would be seen in about 40% of patients having an alert. With a sample size of >1000 (intervention group—Heartlands and area, after phase), a 95% CI of width 6% (37% to 43%) can be calculated. A sample size of 370 (control group—Good Hope and area, after phase) will allow us to produce a 95% CI of width 10% (35% to 45%).

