### Intervention package

The Outreach team will advise on an evidence-based package of care (these interventions are limited to the intervention arm):
*Diagnostic and monitoring recommendations*—to rapidly establish a credible diagnosis of the cause of AKI including:
Improved assessment of volume status;Standardised use of urine dipstick (often missed);Appropriate sepsis investigations;Urgent ultrasound with suspected obstruction, while avoiding early ultrasound in patients at low risk of obstruction.*AKI treatment recommendations*—to treat correctable causes of AKI:
Rapid, limited treatment of hypovolaemia, with avoidance of iatrogenic fluid overload, recently recognised as a significant cause of mortality in AKI;Rapid sepsis therapy;Cessation of potentially nephrotoxic agents (many well known, such as ACE inhibitors and non-steroidal drugs, but others less well known such as Aciclovir);Urgent relief of urinary tract obstruction.*Recommendations to manage the acute illness:*
Where needed, recommendations will be made to address key aspects of the major underlying comorbidity;Improve nutrition, as malnutrition is known to be associated with poor outcome. Dietetic referral will be made for all appropriate inpatients with stage 3 AKI.*Pathway recommendations:*
For inpatients, refer to the Renal and/or Critical Care Outreach teams, as appropriate;For patients in the community, arrange urgent or immediate outpatient review or admission, as appropriate;Arrange formal palliative care when necessary.*Stage-based AKI management:*
Stage 1 patients will typically receive a single intervention call;Stage 2 patients will usually receive a single intervention call and be discussed with the renal consultant;Stage 3 inpatients will be reviewed by a consultant, ideally within 24 hours of the AKI Outreach team being aware of their presence in the intervention hospital (Heartlands Hospital);Rapid AKI follow-up clinic—we will offer surviving patients with stage 3 AKI a rapid follow-up clinic appointment, ideally within 7 days of discharge, or within 7 days of the alert if the patient is not admitted to hospital.

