### Outcomes

The primary purpose of this study is to assess feasibility and inform a full cluster randomised study. The primary outcome for the full study, also collected in this study, is reflected in the trial acronym: deterioration or death of the patient with AKI, and is a combination of:
All-cause death within 30 days;Any need for dialysis or renal replacement therapy (intermittent haemodialysis (typically at the Renal Unit of Birmingham Heartlands Hospital) or continuous renal replacement therapy (typically in the intensive care units of the Trust)) within 30 days;Progression of AKI stage without dialysis within 30 days after the alert (stage progression is stage 1 deteriorating to 2 or 3; stage 2 deteriorating to stage 3).

These were chosen to reflect the major, potentially modifiable, outcomes of concern for patients (death and/or dialysis) and renal units or hospitals (death, dialysis or deterioration). Stage progression (compared to non-progression) is known to be associated with increased mortality and length of stay in a multivariate analysis,^34^ and is a useful surrogate end point.

Secondary outcomes for the main study, collected to assess feasibility here, are as follows:

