**Table d35e730:** 

Measured outcome	Time window
Percentage of patients admitted to hospital	Within 14 days of alert
Percentage requiring any critical care admission	During index admission
Other key events (see below)	During index admission
Percentage discharged to institutional care	After index admission
All-cause mortality	At 90, 182 and 365 days
Renal function (eGFR)	At 90, 182 and 365 days

In a pragmatic study, patients will not be recalled for renal function testing; at the time points above, we will use the last observation carried forward for all living patients. Key events are these events as given in the discharge letter:
Cause of AKI: new glomerulonephritis or new urinary obstruction diagnosis.Complication of AKI not requiring dialysis: new pulmonary oedema, uraemia ≥30 mmol/L or hyperkalaemia (≥6.0 mmol/L).

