### Statistical analysis

The focus of the study is to assess feasibility of all aspects prior to full-scale evaluation. The data collected in this pilot study will be used to assess the uncertainty of the primary outcome. Further analyses will separately compare the before and after arms at the intervention and control sites. We note that the intervention and control sites cannot be directly compared. The control site data will be used to assess any ‘system-wide’ change in AKI outcomes. Additionally, survival analyses will be carried out, examining time to first composite primary outcome, and Kaplan-Meier survival curves produced for each of the four groups. This pilot study is not powered to provide a full comparison of the before and after phases. Among the end points, the use of dialysis and frequency of non-dialytic AKI complications will give an indication of the safety of the intervention. We will analyse estimated Glomerular Filtration Rate (eGFR) and CKD stage at a group level and changes at individual patient level. We will also explore the potential of using these data to validate our previous prognostic index.^9^

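### The complication item used as a safety indicator leaves out complications that required dialysis, so its before/after change mixes complications with dialysis use

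*Protocol article*

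**What the plan says.** Three parts of the protocol article bear on this.

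- **Outcomes, secondary outcome table and the text below it.** The table lists "Other key events (see below"), with the index admission as time window. The source is then fixed: "Key events are these events as given in the discharge letter". One of the two types of key event is "Complication of AKI not requiring dialysis: new pulmonary oedema, uraemia ≥30 mmol/L or hyperkalaemia (≥6.0 mmol/L").
- **Statistical analysis.** The restriction appears again and is given a purpose: "the use of dialysis and frequency of non-dialytic AKI complications will give an indication of the safety of the intervention". The comparison is before against after within each site: "Further analyses will separately compare the before and after arms at the intervention and control sites". The section also says that the pilot is not powered for a full before/after comparison.
- **Outcomes, primary composite.** Dialysis is a component in its own right, "Any need for dialysis or renal replacement therapy", with a 30-day window.

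The Intervention package section gives routes by which Outreach could change dialysis use at Heartlands. One is "For inpatients, refer to the Renal and/or Critical Care Outreach teams, as appropriate"; another is rapid treatment of correctable causes. No listed outcome counts pulmonary oedema, uraemia or hyperkalaemia in patients whose complication required dialysis.

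**The concern.** A safety reading needs to know how often these three complications occur. The stated item gives that frequency after patients who needed dialysis have been removed, and whether a patient is dialysed is settled after the alert, partly through care that Outreach is meant to influence. The numerator is thus selected on a possible effect of the intervention.

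Two misreadings follow. If a larger share of complicated patients at Heartlands is dialysed in the after phase, the item falls although the complications are unchanged; if a smaller share is dialysed, it rises. A real rise in complications can also be offset by a rise in the dialysed share and leave no trace in the item. The control site cannot reveal this, because a shift caused by Outreach would occur only at Heartlands. The Conclusions section makes feasibility and safety the condition for a large cluster trial, and the secondary outcomes are described as those of that main study, so the definition could carry forward.

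**Working it through.** **The plan's own figures.** The plan states no complication rate and no dialysis rate. Its only calculation, in After phase sample size, concerns the composite ("Our previous work suggested that the combined outcome would be seen in about 40% of patients having an alert"). It reproduces: 0.40 ± 1.96 × √(0.40 × 0.60 / n) gives 37.0% to 43.0% for n = 1000 and 35.0% to 45.0% for n = 370. It has no bearing on this point.

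**Set-up.** Let c be the proportion of patients with at least one listed complication, d the share of those patients who are dialysed, and u the proportion dialysed with none of the listed complications. If both windows were the same:

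- stated item: m = c × (1 − d)
- dialysis use: D = c × d + u
- sum: m + D = c + u

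The values of c and d below are assumptions.

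**1. The item moves while complications stay fixed.**

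| c | d before → after | m before → after | relative change |
|---|---|---|---|
| 5% | 10% → 20% | 4.5% → 4.0% | −11% |
| 10% | 10% → 20% | 9.0% → 8.0% | −11% |
| 20% | 10% → 20% | 18.0% → 16.0% | −11% |
| 10% | 10% → 40% | 9.0% → 6.0% | −33% |
| 10% | 20% → 10% | 8.0% → 9.0% | +12.5% |

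The relative change depends only on d: it equals (1 − d after)/(1 − d before) − 1.

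**2. The item stays fixed while complications move.** With c rising from 10% to 12% and d from 10% to 25%, m = 0.10 × 0.90 = 9.0% before and 0.12 × 0.75 = 9.0% after.

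**3. Dialysis use alongside does not recover c.** From the sum, c = m + D − u, and u is not reported. In step 2, dialysis among complicated patients rises from 0.10 × 0.10 = 1.0% to 0.12 × 0.25 = 3.0%, so with u constant D rises by 2.0 points. Now suppose instead that c stays at 10%, d stays at 10%, and u rises by 2.0 points. Again m is 9.0% in both phases and D rises by 2.0 points. The two reported figures are identical, yet complications rose in the first case and not in the second.

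**4. The windows differ.** Dialysis runs to 30 days and key events cover the index admission. Dialysis after discharge but within 30 days enters D only. As stated, therefore, even the sum m + D is not a count over one common period.

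**5. Size against sampling error.** If before-phase recruitment at Heartlands is in proportion to its length (an assumption), 1000 × 2/5 = 400 patients. For 9.0% against 8.0%, the standard error of the difference is √(0.09 × 0.91/400 + 0.08 × 0.92/1000) = 1.7 points. The 1.0-point artefact is about 0.6 of a standard error. With only admitted patients in the denominator the standard error would be larger.

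**The case against.** The strongest reply is that the plan never reads the item alone. The Statistical analysis section names dialysis use in the same sentence, so a patient who moves from complicated-without-dialysis to dialysed lowers one count and raises the other, and both are visible. The primary composite makes a similar split, since it counts stage progression without dialysis. The item is also secondary, collected to assess feasibility, offered only as an indication, and tied to no decision rule.

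Most of this stands, and it limits the weight of the point. It does not dispose of it. In the composite the split is harmless because death, dialysis and progression are joined into one outcome over one 30-day window, so movement between components leaves the total unchanged. The safety sentence instead names two separate frequencies over different windows, states no combined count, and does not allow the complication rate to be recovered (step 3).

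Two stronger readings should be resisted. A reader might infer that the item moves with every change in dialysis use. It does not: dialysis in patients with none of the three complications leaves it unchanged. A reader might also infer that the pilot's safety conclusion will be wrong, or that the distortion is large. The documents give no complication or dialysis rate, so neither its direction nor its size can be established; under the main illustration it is smaller than the sampling error.

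**Conclusion.** The point holds as a minor refinement of a secondary safety indicator. The item depends on a post-alert treatment that Outreach may change, and the same complications in dialysed patients go uncounted. A before/after shift in the item cannot by itself be read as a change in complications, and the accompanying dialysis figure only partly repairs this.

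The defect follows from the wording alone. Its size rests on assumed values: roughly a tenth of the item's value for a dialysed share moving from 10% to 20%, and a third for a move from 10% to 40%. More patients would not cure it, because it is a matter of definition. The point takes no view on when dialysis should be given.

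**What to change.** In the key-event definition and in the safety sentence of Statistical analysis:

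1. Count new pulmonary oedema, uraemia and hyperkalaemia at the stated thresholds, as given in the discharge letter for the index admission, in all admitted enrolled patients, irrespective of dialysis.
2. Do not stop counting at the start of dialysis. Earlier dialysis would then shorten the counting period and bring back the same dependence, and discharge letters may not give the timing needed.
3. Add one combined count, dialysis or any of these complications, with both parts taken over the index admission.
4. Keep dialysis use and the non-dialytic split as descriptive lines.

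The denominator has to be admitted patients, because community patients who are never admitted have no discharge letter. The percentage admitted, already a secondary outcome, should be shown beside it.

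The cost is a change of wording, one extra tabulation, and coding of the three events from the discharge letters of dialysed patients as well. The remaining drawback is that events after dialysis starts may themselves be influenced by dialysis; the combined count and the descriptive split help the reader to judge this.

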#### Alerts

The electronic AKI alerts are the trigger for the afferent arm of the intervention. The alerts are generated within the laboratory software (Telepath, Computer Sciences Corporation) according to the national algorithm.^25^ It compares the current patient creatinine to a value in the past (baseline creatinine). The staging follows KDIGO guidelines for AKI,^26^ where 0 is no AKI and 3 is the most severe stage. Alerts are made visible to all users of the electronic patient records, with the stage being stated as part of all urea, creatinine and electrolyte reports. The alerts from our hospital laboratory also contain a hyperlink to online guidance, with separate guidance for hospital and community alerts. Alerts are not issued for patients in the dialysis units and renal wards. We refer to the current location of the patient when discussing community (primary care) or hospital alerts. Obviously some of the hospital alerts will represent what was community-acquired AKI, but Outreach focuses on the current location of the patient.

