### Discussion and limitations of the study

The national algorithm for staging of AKI means that identification of patients with AKI is standardised. The ‘opt out’ consent process enables large-scale recruitment. The ethos of AKI Outreach is that advice is offered to the primary clinician, who may choose to act upon or ignore that advice. A key challenge in implementing the intervention is reaching and influencing the decision maker(s) within the primary team, especially as they have varying roles and beliefs.

The AKI Outreach service runs only 40 hours/week and not out-of-hours. As this is a pilot for a full CRT, there were only two sites and randomisation was not undertaken. Inevitably, the intervention and the control sites are different to a certain extent. The latter does not have on-site nephrology services. A full CRT is needed to provide a definitive answer regarding any benefits of this approach. What would a successful pilot look like? The delivery of recommendations acceptable to clinicians, comparable to our previous work (median of 3 within a median of 15 hours), and to large numbers of patients is a key indicator of success. The control group should show no evidence of a system-wide change in before and after AKI outcomes. The intervention group will provide evidence of the feasibility and safety of the intervention.

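### Complications used as a safety indication have no time anchor to the alert, so urea or potassium already over threshold on a hospital alert sample may be counted and dilute the before/after comparison

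*Protocol article*

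**What the plan says.** In the protocol article, the table of secondary outcomes under Outcomes gives the window as "Other key events (see below) During index admission". The text below the table says "Key events are these events as given in the discharge letter" and defines the complication group as "Complication of AKI not requiring dialysis: new pulmonary oedema", urea of at least 30 mmol/L or potassium of at least 6.0 mmol/L.

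Statistical analysis gives this group a specific role: "the use of dialysis and frequency of non-dialytic AKI complications will give an indication of the safety of the intervention". The same section compares before and after separately at each site and states that the pilot is not powered for a full comparison of the phases.

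Alerts says that the alert triggers the intervention and is shown on the laboratory report, "with the stage being stated as part of all urea, creatinine and electrolyte reports". Study team limits Outreach to working hours on five days a week. The Discussion gives the benchmark for delivering recommendations as "median of 3 within a median of 15 hours".

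Other outcomes are timed from the alert. The stage-progression component of the primary outcome is counted over 30 days after it, and hospital admission over 14 days from it.

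**The concern.** A measure of the safety of an intervention should count events that the intervention could have caused or prevented. The alert comes from a blood sample whose report also carries urea and electrolytes, and Outreach follows hours later, or after a weekend. If urea or potassium is over threshold on that sample, Outreach played no part in it. The window still admits it, because an admission that contains the alert also contains the alert sample.

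A real rise in complications after Outreach would then be measured against a background of events that Outreach cannot affect, and would be harder to see. This matters beyond the pilot: the Discussion expects the intervention group to supply evidence of safety, and the Conclusions make a finding of feasible and safe the condition for moving to a cluster trial.

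**Working it through.** **Reading the text.** Three features decide which events can be counted.

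1. *Window.* It is the index admission, with no start at the alert.
2. *The word 'new'.* In the complication bullet it stands once, before pulmonary oedema. The bullet on causes of AKI repeats it for each diagnosis, so the natural reading is that it does not reach urea and potassium. Even if it did, it is not defined relative to the alert: a value first found on the alert sample could still be new to the admission.
3. *Setting.* For a community alert followed by admission, the admission starts after the alert, so the alert sample lies outside the window. The gap therefore concerns alerts raised in hospital.

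**Inputs for an illustration.** The article gives no complication rate, no share present at the alert and no before-phase sample size. Its sample-size figures concern the 40% composite outcome. They reproduce (half-width 1.96 × √(0.4 × 0.6/1000) = 0.030, so 37% to 43%) but do not bear on this point. Assumptions:

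- Heartlands after phase: 1000 patients (the article says more than 1000).
- Heartlands before phase: 1000 × 8/20 weeks = 400.
- Total complication rate before, T: 10% or 15%.
- Share of these present at the alert, s: 40%, 60% or 80%, the same in both phases.
- True effect: post-alert complications rise 1.5-fold.

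**Dilution.** The ratio seen is [sT + 1.5(1 − s)T]/T = s + 1.5(1 − s), which does not depend on T. Power is two-sided at 5%, by the normal approximation with unpooled variance. The post-alert analysis drops patients already affected, leaving 400(1 − sT) and 1000(1 − sT) at risk.

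Worked case, T = 10%, s = 60%:

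- All events: 10% → 6% + 1.5 × 4% = 12%. SE = √(0.10 × 0.90/400 + 0.12 × 0.88/1000) = 0.0182; 0.02/0.0182 = 1.10; power 0.20.
- Post-alert events: 0.04/0.94 = 4.26% → 0.06/0.94 = 6.38%, in 376 and 940 patients. SE = 0.0131; 0.0213/0.0131 = 1.62; power 0.37.

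| T | s | Ratio seen (true 1.5) | Power, all events | Power, post-alert events |
|---|---|---|---|---|
| 10% | 40% | 1.3 | 0.37 | 0.52 |
| 10% | 60% | 1.2 | 0.20 | 0.37 |
| 10% | 80% | 1.1 | 0.09 | 0.21 |
| 15% | 40% | 1.3 | 0.54 | 0.71 |
| 15% | 60% | 1.2 | 0.28 | 0.52 |
| 15% | 80% | 1.1 | 0.11 | 0.29 |

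**If the share present at the alert changes between phases.** Let q be the proportion of all patients over threshold at the alert and p the post-alert rate in the rest. The observed rate is q + (1 − q)p.

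- No true effect, p = 5% in both phases, q rising from 5% to 8%: 0.05 + 0.95 × 0.05 = 9.75%, then 0.08 + 0.92 × 0.05 = 12.6%. The ratio is 1.29.
- True rise in p from 5% to 7.5%, q falling from 5% to 2.5%: 9.75%, then 0.025 + 0.975 × 0.075 = 9.81%. The ratio is 1.01.

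These two cases show direction only; the values of q are assumed.

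**The case against.** A reader might infer that complications present at the alert are routinely scored as safety events, for all three complications and all patients. The documents do not support that. Pulmonary oedema is qualified as new and is not read from the blood sample, community alerts that lead to a later admission fall outside the problem, and an event counts only if the discharge letter gives it. The supportable wording is that such events may be counted, for urea and potassium, in patients with a hospital alert.

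A reader might also infer that the definition itself produces a false signal of harm. It does not. One definition serves all four groups, and comparisons are within site. A constant share present at the alert pulls a real ratio towards 1 but leaves a null comparison null. Mimicry or masking needs that share to shift between phases. The article concedes more recurrent AKI in the before phase but reports no difference in urea or potassium at the alert. The control site offers a check on system-wide change, though not on a shift confined to Heartlands.

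The article also claims only an indication of safety, from an unpowered pilot with dialysis as a second measure, and even the corrected indicator has power of only 0.21 to 0.71 in the table. This stands, and it limits the weight of the point. It does not justify a window that adds events Outreach could not affect.

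Finally, a rule for values already abnormal at enrolment might sit in the full protocol or analysis plan. But the article does more than leave a detail open: it states a window, and that window is unsuited to the use made of it.

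**Conclusion.** The point holds in a limited form. As stated, the window lets urea or potassium over threshold on a hospital alert sample count towards a safety indication, provided that the discharge letter records it. The consequence is dilution of the before/after comparison at each site. Any mimicking or masking of harm is conditional on a change in presenting severity between phases.

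The size cannot be computed from the documents. Under the assumed rates and 400 v 1000 patients, a true ratio of 1.5 would be seen as 1.1 to 1.3; the result follows directly from the assumed share present at the alert. Since the safety reading is descriptive, this is a moderate defect that is worth correcting and does not undermine the pilot.

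**What to change.** In all four groups, base the safety indicator on complications first recorded after the alert sample. Use dated urea and potassium results, and restrict each laboratory complication to patients not already over that threshold at the alert. The alert is the workable time origin because every group has one; only the Heartlands after-phase group has an Outreach call. Report complications present at the alert separately as baseline severity. Keep the all-admission frequency as a descriptive figure, so that worsening in patients already affected is not hidden.

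The cost is a short change to the outcome definition, some extra extraction of dated results and fewer counted events. Two limits remain. Events between the alert and the Outreach call still count. A change in presenting severity between phases is only partly removed, since sicker patients would also be expected to have more complications after the alert.
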